## Abstract

Perinatal depression (PD) is a severe and disabling condition impacting negatively on children in terms of adverse neonatal outcomes and on the well-being of women and their families. All pregnant women attending the unit of Gynecology and Obstetrics Service of the University of Campania “L. Vanvitelli” will be screened for PD using the Edinburgh Postpartum Depression Scale (EPDS). Women with a score ≥10 at the EPDS will be invited to receive a full psychiatric assessment. The required sample size is of 126 women with PD which will be randomly allocated to either an experimental group, receiving a uni-familiar psychoeducational intervention, or to a control group, receiving the Best Treatment Option (BTO). Patients will be evaluated through several assessment instruments: Hamilton Depression Rating Scale (HAM-D), Hamilton Anxiety Rating Scale (HAM-A), Global Assessment of Functioning (GAF), Clinical Global Impression (CGI), Manchester Short Assessment of Quality of Life (MANSA), Family Assessment Device (FAD), Family Coping Questionnaire (FCQ), and Pattern of Care Schedule (PCS). Patients will be evaluated at baseline, 3, 6, 9, and 12 months post-randomization. The severity of depressive symptoms at the HAM-D scale has been selected as primary outcome. Other outcome measures include improvement in the severity of anxiety symptoms, of global and personal functioning, an improvement in family members' coping strategies and in the level of quality of life. It has been highlighted the importance of developing screening and treating programs for PD, and our study will use rigorous study design to evaluate the efficacy of the adaption of a well-known family psychoeducational model to the treatment of PD. The aims of present trial are to: (1) develop an informative package for pregnant women with PD; (2) promote a screening programme for PD; (3) identify those (socio-demographic and pregnancy-related environmental) factors associated with a higher risk to develop a perinatal or postnatal depression; (4) evaluate the efficacy of a new experimental psychoeducational intervention in reducing the depressive symptoms during pregnancy compared to the BTO.

## Introduction

Depressive disorders represent the major cause of disability worldwide (1, 2). These disorders are prevalent in the perinatal period and about 12% of women are affected (3). However, prevalence rates of perinatal depression (PD) should be cautiously considered since this disorder is frequently underdiagnosed, mainly because patients experience delays and difficulties in help-seeking due to feelings of guilty and fear of stigmatization (4, 5). PD poses a significant burden on affected women, their families and on society at large; moreover, it carries serious long-term consequences on the mental health of the new born (6, 7). In particular, PD can have several detrimental effects including low birth weight, preterm birth, small development for gestational age, early childhood developmental delays, poor maternal fetal attachment, impairments in cognitive functioning, behavioral disturbances, and development of depressive disorders in the childhood or adolescence (8–16).

Different risk factors have been identified for PD, including low socioeconomic status (17–19), being a single mother (17, 20), poor social support (21), general life stress (17), and unplanned pregnancies (22). Indeed, PD is associated with a dysregulation and hyperactivity of the hypothalamic-pituitary-adrenal axis activity (HPA) (23), with an increased exposition to the corticotrophin-releasing hormone (CRH) during intrauterine development.

Several interventions have been developed for reducing the impact of risk factors and for preventing the development of PD (24), including professionally-based home visits, postpartum peer-based telephone support, interpersonal psychotherapy (25), and cognitive behavioral therapy (26). Although several of these interventions have been made available in clinical practice, research is needed in order to confirm their efficacy (27).

Symptoms of perinatal depression often include anxiety, irritability, sleep disturbance, low mood, and excessive concern for the child's care (28), in fact, PD is a multi-faceted and complex condition which can have heterogeneous clinical presentations (15). In particular, a significant number of women with PD experience comorbid anxiety (29, 30), obsessive-compulsive symptoms and post-traumatic stress disorders (31).

One of the main debated issues regarding the optimal prevention and treatment of perinatal depression is related to the opportunity to early detect the disorder through screening procedures (32, 33). In particular, it has been argued that screening programmes can be effective in reducing burden and disability associated with the disorder (34), although there is the risk to create false-positives (35). Screening procedures aim to detect people at high risk to develop a full-blown disorder, and therefore the clinical utility of the screening process is greatly influenced by the ability to accurately identify those patients (33–35).

However, screening programmes are considered acceptable and even desirable by most pregnant women, both depressed and non-depressed (36). Therefore, available guidelines (37, 38) recommend that healthcare professionals (including midwives, obstetricians, health visitors, and general practitioners) ask questions about past or present mental illness, family history of perinatal mental illness and previous psychiatric treatments including inpatient care. Moreover, the American Academy of Pediatrics also recommend that pediatricians screen new mothers for depression during their visits in the 6 months following childbirth (39).

According to a recent review (40), treatment of PD depends on symptom severity and functional impairment (41, 42). Cognitive behavioral therapy (43), interpersonal psychotherapy, and psychoeducation (44, 45) are usually adopted in case of mild to moderate forms of PD; while antidepressants, more often selective serotonin reuptake inhibitors (SSRI), are used for severe cases (46–51).

When available, pregnant women with PD prefer psychotherapy (52) and the effectiveness of psychological and psychosocial treatments for PD has been explored (53).

Several initiatives have been proposed worldwide in order to assess the efficacy and feasibility of psychoeducational interventions for women with PD. A recent meta-analysis by Sockel (26) found only one study (54) evaluating the efficacy of a psychoeducational programme for women with PD in improving depressive symptoms. More recently, other programmes have been proposed also in low-middle income countries (55).

Psychoeducational interventions are effective in reducing affective symptoms and the levels of stress, with low costs for the mental health department (56).

Based on these premises, the Department of Psychiatry of the University of Campania “Luigi Vanvitelli” is carrying out a study to develop and test the efficacy of a psychoeducational family intervention in pregnant women with perinatal depression and their close relatives.

To our knowledge no randomized controlled trial has been carried out so far in Italy on the effectiveness of psychoeducational interventions for women affected by perinatal depression, although psychoeducational intervention has demonstrated its efficacy in a wide range of severe mental disorders, such as bipolar disorder (57), schizophrenia (58), major depression (59), obsessive compulsive disorder (60), and eating disorders (61).

## Aims

The present trial aims to evaluate the efficacy and feasibility of a new psychoeducational family intervention compared to the Best Treatment Option (BTO) in a sample of women affected by perinatal depression and their family members. The Best Treatment Option (BTO) is provided according to the NICE guidelines (62). In particular, mild to moderate forms of depression may be addressed with self-help or psychological counseling. For moderate or severe forms of PD, high-intensity psychological intervention, or pharmacological treatments are recommended.

The secondary aims are to: (1) improve mental health literacy on the topic of perinatal depression, with a specific focus on risk and protective factors as well as on available therapeutic strategies for the management of perinatal depression; (2) identify clinical, socio-cultural, and pregnancy-related predictive factors for the development of perinatal depression; (3) improve coping strategies and family functioning of family members participating to the intervention; (4) evaluate the long-term effects of the intervention.

## Methods

### Design

This is a randomized controlled trial with two parallel arms for evaluating the efficacy and effectiveness of psychoeducational family intervention in improving depressive symptoms in patients with perinatal depression. The new psychoeducational intervention has been developed by the research staff, based on the Falloon model of psychoeducation for patients with schizophrenia and their families (63).

## Patients' Recruitment Procedure

Recruitment for the RCT will be conducted adopting a multistep strategy, as reported in Figure 1:
- Step 1. All pregnant women attending the outpatient unit of Gynecology and Obstetrics of the University of Campania “Luigi Vanvitelli” will be invited to participate in the study through the use of informative leaflets on perinatal depression (i.e., characteristics of the disorder, risks, long-term consequences, available treatments). Those interested in having more information will be referred to a research team member presenting a brief overview of study procedures and time commitment in order to obtain their informed consent. Once informed consent is obtained, patients will be officially enrolled in the study and will undergo the screening procedure, compiling the Edinburgh Postnatal Depression Scale (EPDS) (64).- Step 2. Women with a score ≥10 at the EPDS will be invited to receive a full psychiatric assessment.- Step 3. Patients will receive a full mental state examination by an expert clinician working at the Department of Psychiatry of the University of Campania “Luigi Vanvitelli,” in order to evaluate the presence of any mental disorder.- Step 4. Once a diagnosis of perinatal depression is made, patient's code will be given to the statistician for randomization in one of the two groups. Patients will be allocated through a randomized procedure (with a 1:1 ratio) to the experimental or to the control group.

**Figure 1 F1:**
[figure not shown]
Multi-step recruitment procedure.

## Inclusion Criteria

Starting from January 2019, patients attending the outpatient unit of Gynecology and Obstetrics of the University of Campania “Luigi Vanvitelli” will be invited to participate to the study. The eligibility criteria will be: (1) gestation age > 3 months or within 3 days of childbirth; (2) age ≥ 18 years; (3) absence of any disabling physical condition; (4) living with a relative for at least 9 months in the last year and continuously in the last 3 months.

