## Assessment Time and Instruments

Researchers participating to the study are blinded to patient allocation. All patients are assessed at the following time points: baseline (T0); 3 months post-randomization (T1); 6 months post-randomization (T2); 9 months post-randomization (T3); 12 months post-randomization (T4) (Table 2).

**Table 2 T2:** Assessment tools adopted in the study's protocol.

	**Screening phase**	**T0 (baseline)**	**T1 (month 3)**	**T2 (month 6)**	**T3 (month 9)**	**T4 (month 12)**

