### Data Analysis

Differences in socio-demographic and clinical characteristics, such as severity of depressive and anxiety symptoms, quality of life, trimester of pregnancy, and personal functioning between the two groups will be evaluated using Chi-square or *T*-test for independent samples, as appropriate. Differences in coping strategies and in family accommodation reported by relatives will be evaluated with the same tests.

In order to assess the efficacy of the experimental intervention, a linear multivariable regression model will be implemented, using as main outcome the score at HAM-D at 3 months post-randomization. Moreover, several confounding variables (such as age, marital status, familiarity for mental disorders, peer support, previous pregnancy, etc.) will be entered in the model. Furthermore, predictors of response at the end of the intervention will be identified.

“Response” is generally defined as a 50% decrease in scores on Hamilton Depression Rating Scale (HAMD) (74). In this protocol, we will consider the score at the 3-month HAM-D compared with the baseline score. Therefore, the continuous variable “3-month HAM-D score” will be transformed in a binary variable (1 = response; 0 = absence of response), and it will be entered in a logistic regression multivariate model in order to identify possible predictors of positive response to the experimental intervention.

In order to evaluate differences in relatives' coping strategies according to patients' clinical features and type of relationship with the patient, a two-level model with fixed independent variables and random intercept, using a maximum likelihood estimation, will be performed. The mean score at the subscales of the FCQ will be entered in the model, adding covariates step by step in order to identify the model with indexes of best fit. The final model will be selected according to the−2 loglikelihood value, and the model with the lowest value will be choose. Estimate, standard error, 95% confidence interval, and *P*-values will be calculated.

The level of significance will be set at *p* < 0.05. All analyses will be performed using the Statistical Package for Social Science software (SPSS), version 18.0 (SPSS).

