One of the main strengths of our study is represented by the adaption of a well-known family psychoeducational model to the treatment of perinatal depression. In particular, the Falloon psychoeducational intervention was developed for the community management of schizophrenia (63, 90) and has been subsequently adapted to the management of major depression (59, 91) and bipolar disorder (57, 92–94). Perinatal depression may represent an ideal target for this kind of interventions, since it is highly dependent from stressful life events and from family context. Moreover, peripartum is a period of women's life in which pharmacological treatments should be used very cautiously and only in a limited situations. Another strength of our study is the rigorous methodology adopted, which will allow us to understand the impact of the experimental intervention on patient's outcome through a randomized controlled approach. Moreover, the main outcome is the reduction of depressive symptoms at 3-months after randomization. This is an ambitious outcome, since many confounding variables can impact on it. In particular, in some cases the childbirth represents itself an event associated with a reduction of depressive symptoms (95), thus biasing the effectiveness of the experimental intervention. Moreover, other contextual factors (such as support by family members, changes in the daily routine following the childbirth, or starting a pharmacological treatment) can have an impact on the long-term outcome. We aim to control for such variables using a statistical procedure, in order to accommodate for the impact of all these confounding variables.

Furthermore, the postnatal psychoeducation programme is suitable for clinical use as it is relatively brief and can be delivered by postnatal unit nurses and midwives after a short period of training.

Another strength of this study is the use of the EPDS as screening measure, which will allow comparisons with data from other international studies.

In order to detect patients affected by both major and minor depression, the cut-off at EPDS of ≥10 has been selected (71) and it will have to be complemented by the clinical judgment (96).

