The assessment tools have been selected on the basis of their wide use in clinical practice and in clinical trials (84). Therefore, the adoption of these instruments will give us the opportunity to compare our findings with those of other previous studies. Moreover, the HAM-A and HAM-D are well-known, validated, reliable, and easy to use scales, and have been selected in order to not overburden the researchers and mental health professionals involved in the study with a specific training on the use of assessment tools (84).

Our study has some limitations. The first is the fact that the study will be carried out in one center only, with a consequent reduced generalizability of findings. However, this can be considered as a pilot study representing the basis for a larger multicentric study that our research group is planning.

Another possible limitation is the exclusion from the study of women with psychotic disorders or women with depressive disorders before pregnancy. This methodological choice was due to the need to assess and treat only patients with an onset of depression during pregnancy. Another possible limitation is the lack of a standardized pharmacological treatment for women that will be recruited for the RCT phase. Despite a standardized pharmacological treatment could be useful to assess more precisely the efficacy of the experimental psychoeducational intervention, we decided not to standardize the pharmacological treatment in order to treat women with PD under ordinary conditions. In any case, the pharmacological management of pregnant women will follow the NICE guidelines (62).

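### The abstract's efficacy aim is limited to symptoms during pregnancy, but the entry window and a 3-month rating counted from randomization put much of T1 after birth; stage at entry is not a named covariate, and the Discussion's promised adjustment could reach post-randomization events

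*Protocol article*

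**What the plan says.** **Aim.** The Abstract gives aim 4 as to "evaluate the efficacy of a new experimental psychoeducational intervention in reducing the depressive symptoms during pregnancy compared to the BTO". The Aims section is wider: it evaluates the intervention "in a sample of women affected by perinatal depression and their family members", with no limit to pregnancy. The Design section likewise refers to perinatal depression.

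**Entry.** The first eligibility criterion is "gestation age > 3 months or within 3 days of childbirth".

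**Timing.** Assessment Time and Instruments, Data Analysis and Primary Outcome all place the primary HAM-D rating 3 months after randomization. None of them ties it to delivery.

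**Covariates.** For the linear model of the 3-month score, Data Analysis says that "several confounding variables (such as age, marital status, familiarity for mental disorders, peer support, previous pregnancy, etc.) will be entered in the model". Trimester appears there only among the characteristics compared between groups. Gestational period is collected at baseline (Baseline Assessments, Table 3).

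**Childbirth.** The Discussion notes that "in some cases the childbirth represents itself an event associated with a reduction of depressive symptoms" and regards this as a threat to the result. It adds family support, changes in routine after the birth and the start of drug treatment as further influences. It then states an intention to control for such variables by a statistical procedure that it does not specify.

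**The concern.** Two things do not fit together.

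First, a rating fixed at 3 months from randomization cannot fall in pregnancy for a woman who enters late in gestation or after delivery. A T1 result from such a sample mixes antenatal and postnatal ratings. It cannot support a conclusion confined to pregnancy, which is how aim 4 is worded.

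Second, the protocol singles out childbirth as an influence on the outcome but does not name the baseline variable that would handle it cleanly, namely stage at randomization. What it does announce is control of a group of variables that, for women enrolled in pregnancy, include events after randomization. The intervention works on family communication and problem solving, and it discusses treatment options and adherence (Features of the Experimental Intervention). Family support and the start of medication may therefore be affected by allocation. Adjusting for their later values could remove part of the treatment effect or introduce bias into a randomized comparison.

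**Working it through.** **1. The plan's own figure.** Inputs from Power Analysis: effect size 0.65, α 0.05, power 0.95, 1:1 allocation. A two-sided two-sample t-test (noncentral t) needs 62.49 per arm, rounded up to 63, so 126 in total. This matches the plan, and power at 63 per arm is 0.952. The sample size is not in dispute.

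**2. Who is still pregnant at T1.** Assumptions not in the documents: term at 40 weeks, 3 months taken as 13 weeks, antenatal entry even over weeks 13 to 40.

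- Latest entry week for a rating in pregnancy: 40 − 13 = 27.
- Share still pregnant at T1, antenatal entrants only: (27 − 13)/(40 − 13) = 14/27 = 52%. The other 48% have delivered.
- If a share p enters postpartum, the share still pregnant is 0.519 × (1 − p):

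| Postpartum entrants (assumed) | Still pregnant at T1 | Rated after birth |
|---|---|---|
| 0% | 52% | 48% |
| 10% | 47% | 53% |
| 25% | 39% | 61% |
| 50% | 26% | 74% |

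With a 38-week term and no postpartum entry, the share still pregnant is 12/25 = 48%. The result depends on the entry pattern: if all enter by week 27, everyone is still pregnant at T1; if all enter from week 28, no one is.

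**3. What omitting stage costs in precision.** Assume half have delivered by T1, a shift of s SD in HAM-D between stages, and a within-stage SD of 1. Variance added = 0.25 s². Share of total variance = 0.25 s²/(1 + 0.25 s²). Standardized effect without adjustment = 0.65/√(1 + 0.25 s²). For s = 0.5 these are 0.0625, 0.0625/1.0625 = 5.9%, and 0.65/√1.0625 = 0.631.

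| Shift s (assumed) | Share of variance | Power at 63 per arm, stage omitted |
|---|---|---|
| 0.2 | 1% | 0.950 |
| 0.5 | 6% | 0.940 |
| 0.8 | 14% | 0.919 |
| 1.0 | 20% | 0.899 |

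Against 0.952, the loss at s = 0.5 is about 1 point. The confidence interval is √1.0625 = 1.03 times as wide.

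**4. Chance imbalance.** For a 50:50 factor with 63 per arm, the SD of the between-arm difference in proportions is √(0.25 × 2/63) = 0.089, and the 95% range is ±1.96 × 0.089 = ±0.175. With s = 0.5, one SD of imbalance moves the estimate by 0.089 × 0.5 = 0.045 SD, and the edge of the 95% range by 0.175 × 0.5 = 0.087 SD. The standard error of the treatment effect is √(2/63) = 0.178 SD.

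**5. Results by stage.** Half the sample is about 31 per arm. Power for an effect of 0.65 is then 0.71, so a breakdown by stage is descriptive only.

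**The case against.** The strongest reply is that enrolling across the perinatal period and timing T1 from randomization is a coherent design, and that the mismatch lies in the wording of the Abstract. The Aims, Design and Primary Outcome sections do not restrict efficacy to pregnancy. That is right, and it is why the remedy is to change the aim and not the design. The document still states two different targets.

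A second reply is that the covariate list is open, the Discussion says childbirth will be dealt with, and a closed list is usually left to the analysis plan. This also stands in part: one can say only that stage is not named. But the article chose to give examples and to announce an adjustment. As described, that adjustment does not separate baseline variables from later events. The procedure is unspecified, so the harm is a risk and not an established error.

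Four stronger readings are tempting, and the documents do not support them.

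- *T1 does not measure symptoms in pregnancy at all.* It does for women randomized before about week 27.
- *The main source of variation is left out.* No variance figure is given. Under the assumptions above, stage explains 1% to 20%. Baseline HAM-D, also not named, would explain 25% at an assumed correlation of 0.5.
- *The estimate is systematically biased.* Randomization balances stage in expectation, and chance imbalance is already reflected in the standard error.
- *The Discussion's rationale of including "only patients with an onset of depression during pregnancy" contradicts the entry window.* That sentence concerns onset and explains the exclusion of earlier depression. A woman entering within 3 days of birth can satisfy it.

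**Conclusion.** The point holds in limited form and should be acted on. Aim 4 in the Abstract is narrower than what T1 can answer: about half the women would be rated after birth if antenatal entry is even, and more if postpartum women enrol. That share rests on an assumed 40-week term, 13-week interval and entry pattern. Recruitment is described as inviting pregnant women, so the postpartum share may be small. The qualitative conclusion needs none of these assumptions, because a postpartum entrant cannot be rated in pregnancy 3 months later.

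On the model, naming stage at randomization is a better way to meet the protocol's own worry about childbirth than an unspecified adjustment that may reach post-randomization events. The benefit lies mainly in interpretation and in avoiding that conditioning. In precision it is small, about 1 point of power at an assumed shift of 0.5 SD.

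**What to change.** 1. Reword aim 4 in the Abstract to perinatal depressive symptoms 3 months after randomization, in line with Aims, Inclusion Criteria and Primary Outcome. The onset rationale in the Discussion needs no change.
2. In Data Analysis, name stage at randomization as a baseline covariate in the primary 3-month HAM-D model: gestational period, with an indicator for women already postpartum at entry.
3. State there, and amend the Discussion to agree, that childbirth after randomization and other post-randomization events (changes in routine, later changes in family support, start of medication) are not adjusted for in the primary analysis.
4. Show the T1 results by stage at randomization descriptively, without subgroup claims.

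The cost is some wording, one variable that is already collected, and one or two degrees of freedom out of 126 women. The postpartum indicator may be sparse if few women enter after birth.
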